#### Secondary outcomes

Completeness of collection of trial endpoints including the percentage of completed weight measurements, 4-day food diaries and International Physical Activity Questionnaire (IPAQ) scores.Fidelity of delivery of the interventions will be measured through the number and modality of completed planned patient contacts, electronic and paper food diaries, and self-reported capillary glucose and ketone measurements.Qualitative analysis of the acceptability and implementation of the interventions will be explored among a subset of participants (~10 in each group) and HCPs through in-depth interviews.

#### Exploratory outcomes

The following outcomes will be explored without statistical inference.

Maternal outcomes:The percentage of women requiring metformin and/or insulin.Four-point capillary glucose profiles during the third trimester (four times daily until delivery).Change in fasting blood test results between baseline measurements, 36–37 weeks gestation, and 12 weeks post delivery (including oral glucose tolerance tests).Mode of delivery, development of preeclampsia, polyhydramnios (maximum liquor volume pool depth ≥8 cm).Quality of life and health status questionnaires (World Health Organisation Quality of Life (Brief Version) (WHOQoL-BREF) and 36-Item Short Form Survey (SF-36) questionnaires).^35 36^
Foetal outcomes:Foetal weight.Gestational age at delivery.

### Measurements

The full schedule of assessments can be found in figure 3.

**Figure 3 F3:**
[figure not shown]
Schedule of assessments.

### Physical measurements

Height, weight and blood pressure will be measured using standardised calibrated equipment in antenatal clinic.

### Blood samples

Fasting venous blood samples will be collected to assess maternal HbA1c, fasting glucose, insulin, beta-hydroxybutyrate, liver function tests, free fatty acids, thyroid function tests and full blood count. At the end of the study, all samples will be disposed of in accordance with the Human Tissue Act (2004).

### Questionnaires

Participants will be asked to complete four questionnaires at four time points throughout the trial (self-reported). Quality of life and health status will be assessed using the WHO Quality of Life Questionnaire (brief version) and the 36-Item Short Form Survey, respectively.^35 36^ Physical activity will be measured using the IPAQ—Short Form, and diet quality will be assessed using the UK Diabetes and Diet Questionnaire.^37 38^ These questionnaires are self-reported by participants and have been chosen as they are widely used and validated tools.

### Food diaries

4-day dietary records will be completed using Libro (Nutritics Mobile Application) or paper food diaries, which will be entered into Nutritics software (Nutritics, Dublin, Ireland).^39^ Participants who wish to use Libro will receive one-to-one training to use this by the study dietitian. Diaries will provide the research team with information about the intake of energy, carbohydrate, fat, protein, fibre, GI and the timing of meals for participants in both groups. Participants will be asked what other dietary modifications, if any, they have made at their fortnightly dietitian reviews to establish the adoption of any alternative dietary practices in the cohort.

#### Adverse events

Participants in both groups will be asked about any adverse effects that they have experienced at each visit. These will include, but are not limited to, the potential effects of a low-energy diet, for example, headache, lethargy, dizziness, constipation, indigestion, poor concentration and hunger. Adverse events will be graded as per CTCAE V.5.^34^ Participants will be issued with a participation/emergency card with emergency contact details for the research team to be carried at all times and to be shown to the attending physician in case of emergency admission to hospital. All participants will be issued with clear instructions as to how to manage a hypoglycaemic and/or ketonaemic event (online supplemental file 5).

10.1136/bmjopen-2023-078264.supp5Supplementary data

#### Data management

Participant data will be anonymised and will be stored in line with the Medicines for Human Use (Clinical Trials) Amended Regulations 2006 and the Data Protection Act (2018) and archived in line with the Medicines for Human Use (Clinical Trials) Amended Regulations (2006) as defined in the MFT Clinical Trials Office Archiving SOP (11; Retention of Data, Off-Site Archiving, and Destroying Documents). Deidentified data will be stored in a study-specific Research Electronic Data Capture database. The sponsor will periodically audit the site study file, a sample of the case report form, consent forms and source data, and check accuracy of the study database to ensure satisfactory completion.

#### Statistical methods

A statistical analysis plan specifying the full details of the primary and secondary outcomes, other variables and methods will be produced prior to trial analysis. The main analysis will be conducted via intention-to-treat population and will not undertake any significance tests. Descriptive, graphical (summary) and basic statistics (eg, (1) number, frequencies and percentages, (2) mean and SD, or (3) median and quartiles as appropriate) will be presented as appropriate for each group, respectively, for group difference jointly, and for each stratum. Per-protocol analysis will be considered as a secondary analysis. Levels of missing data will be investigated and used to inform future studies. No imputation will be used. The end of study questionnaire will be analysed using appropriate descriptive statistics for closed questions and key themes will be extracted without formal analysis from open questions to inform future research.

#### Progression criterion

The success of the feasibility trial will be defined by the progression criteria as outlined in table 1. Any concerns regarding a low retention rate will be discussed with the PPIE group. Interviews will include those who withdraw from the study to address potential reasons for withdrawal with the aim to improve retention in future.

**Table 1 T1:** Trial progression criterion

	Feasible (green)	Feasible with modification of the protocol (amber)	Not feasible (red)
Recruitment	≥4 patients/month	>2 patients/month	≤2 patients/month
Uptake to the feasibility study	≥15%	10%–15%	<10%
Retention to the feasibility study	>70%	50%–70%	<50%
Adherence to the ILED intervention	>50% of the low-energy days completed (2 /week between weeks 24-30 and delivery)	30%–50% of the low-energy days completed (2 /week between weeks 24-30 and delivery)	<30% of the low-energy days completed (2 /week between weeks 24-30 and delivery)

ILED, intermittent low-energy diets.

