**Method and analysis:**

We aim to recruit 48 women with GDM diagnosed between 24 and 30 weeks gestation from antenatal clinics at Wythenshawe and St Mary’s hospitals, Manchester Foundation Trust, over 13 months starting in November 2022. Participants will be randomised (1:1) to ILED (2 low-energy diet days/week of 1000 kcal and 5 days/week of the best NHS care healthy diet and physical activity advice) or best NHS care 7 days/week until delivery of their baby. Primary outcomes include uptake and retention of participants to the trial and adherence to both dietary interventions. Safety outcomes will include birth weight, gestational age at delivery, neonatal hypoglycaemic episodes requiring intervention, neonatal hyperbilirubinaemia, admission to special care baby unit or neonatal intensive care unit, stillbirths, the percentage of women with hypoglycaemic episodes requiring third-party assistance, and significant maternal ketonaemia (defined as ≥1.0 mmol/L). Secondary outcomes will assess the fidelity of delivery of the interventions, and qualitative analysis of participant and healthcare professionals’ experiences of the diet. Exploratory outcomes include the number of women requiring metformin and/or insulin.

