### Trial setting and recruitment

Participants will be recruited from antenatal clinics at Wythenshawe and St Mary’s Hospitals, Manchester Foundation Trust (MFT) between November 2022 and December 2023. This is an urban area within Greater Manchester, and MFT serves patients from a wide range of minority ethnic and sociodemographic backgrounds. Women may self-refer to the antenatal clinic or be referred by their primary care team. Assessments will be carried out at MFT, or remotely if required by COVID-19 restrictions. The qualitative substudy will be carried out at MFT, remotely, or at a location of the participant’s choosing. We aim to recruit eligible participants over a period of 13 months. Potential participants will be given written information about the study and the opportunity to ask questions about the study prior to providing written consent (online supplemental files 1 and 2).

10.1136/bmjopen-2023-078264.supp1Supplementary data

10.1136/bmjopen-2023-078264.supp2Supplementary data

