#### Sample size

We plan to recruit 24 participants per study arm (n=48) which, when considering an estimated attrition rate of 15%, will provide complete outcome data on 40 participants.^24–26^ It has been estimated that 24 participants per group will be sufficient to determine study outcomes, in line with sample size recommendations for feasibility studies.^27–29^

This number will allow us to enable estimation of recruitment/retention parameters with sufficient precision. For example, based on 40 completed participants, it will enable recruitment rates in the region of 25% to be estimated with an error of ±13.42% at most; retention of 85% will be estimated with error of ±11.07% at most. It is also sufficient for estimation of variability (eg, SD) in gestational weight gain and capillary glucose concentrations (proposed outcomes for the future definitive trial) with negligible bias.^30^

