### Outcomes

#### Primary outcomes

Uptake rate measured as a percentage of eligible participants who consent to take part, including the proportion of women who were screened who did not meet the eligibility criteria, and the number of women who did not give consent to take part.Recruitment rate measured as the number of eligible participants who consent to take part per month.Retention rate measured as the number of randomised participants who complete the trial (those who attend the final visit) and the percentage of participants who attend all eight visits.Adherence to the dietary interventions assessed from self-reported adherence to the potential low-calorie days between randomisation and delivery.Completion of self-assessed glucose and ketone readings assessed as a percentage of the required readings.Safety outcomes:Percentage of women following ILED/best NHS care with hypoglycaemia (episodes of blood glucose of <3.0 mmol/mol) and hypoglycaemia requiring third-party assistance as measured by participants.Percentage of women who develop significant ketonaemia in both groups (defined as ≥1.0 mmol/L) as measured by participants.Percentage of neonatal hypoglycaemic episodes requiring intervention (blood glucose checked 2 hours post delivery and 2 hours thereafter for 12 hours according to local protocol), neonatal birth weight, gestational age at delivery, hyperbilirubinaemia/jaundice and/or admission to Special Care Baby Unit or neonatal intensive care, and stillbirths.The incidence and rate of other adverse events (eg, headaches, lethargy, constipation or complications requiring hospital admission) between the start of the trial intervention and delivery recorded as mild, moderate and severe, as defined by Common Terminology Criteria for Adverse Events (CTCAE V.5).^34^ Hospital admission for routine labour and delivery will not be classified as an adverse event.

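### Table 1 sets green recruitment at 4 or more women per month, but the stated plan of 48 women in 13 months is 3.69 per month, so recruiting exactly to plan is graded amber

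*Protocol article*

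**What the plan says.** The abstract (Method and analysis) gives the target and the period: "We aim to recruit 48 women with GDM diagnosed between 24 and 30 weeks gestation", "over 13 months starting in November 2022". The Sample size section repeats the target as 24 per arm. Trial setting and recruitment repeats the period, "We aim to recruit eligible participants over a period of 13 months", and places it "between November 2022 and December 2023".

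Under Primary outcomes, the rate is defined as follows: "Recruitment rate measured as the number of eligible participants who consent to take part per month".

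The Progression criterion section says that Table 1 defines whether the feasibility trial has succeeded. For recruitment, green is "≥4 patients/month", amber is ">2 patients/month" and red is 2 per month or fewer. The article states no planned monthly rate, so that rate has to be derived from the target and the period.

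**The concern.** A progression threshold should agree with the plan it is used to judge, or the document should explain why it does not. Here the target and timetable imply a monthly rate below the green line. The recruitment criterion would then return amber for a trial that did what it set out to do.

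Recruitment rate is a primary outcome, and the trial exists to inform a larger randomised trial. An amber grade produced by a mismatch between the table and the timetable could be read as evidence that recruitment procedures need changing. If the mismatch were noticed only after the data were in, relabelling the result as green would look like a post hoc adjustment.

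**Working it through.** **Inputs**

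- Target: 48 women (abstract; Sample size).
- Recruitment period: 13 months (abstract; Trial setting and recruitment).
- Rate: eligible women who consent, per month (Primary outcomes).
- Cut-offs: green at 4 or more per month, amber above 2, red at 2 or fewer (Table 1).

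**The plan's own figures**

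The sample size statements reproduce. With 15% attrition, 48 × 0.85 = 40.8, in line with the stated 40 completers. The 95% half-widths on 40 women are 1.96 × √(0.25 × 0.75/40) = 13.42% and 1.96 × √(0.85 × 0.15/40) = 11.07%, as printed. The target of 48 is therefore coherent with the rest of that section; the conflict lies between it, the period and Table 1.

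**Planned rate against the green line**

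- Planned rate = target / months = 48/13 = 3.69 per month. This is above 2 and below 4, so amber.
- Shortfall = 4 − 3.69 = 0.31 per month.
- Women needed for green in 13 months = 4 × 13 = 52, which is 4 more than the target (4/48 = 8.3%).
- Months allowed for green with 48 women = 48/4 = 12, one month less than the stated period.
- If November 2022 and December 2023 are both counted in full, the window is 14 months and the rate is 48/14 = 3.43, also amber. The article twice says 13 months, so 3.69 is the figure to use.

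The amber cell has no printed upper bound and so literally overlaps green. This does not affect the result, because 3.69 satisfies only amber.

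**Chance of green at the planned rate (illustration, assuming Poisson accrual)**

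- Recruitment not stopped at 48: the 13-month count has mean 48, and P(52 or more) = 0.300.
- Recruitment stopped at 48: green needs the 48th woman within 12 months. The 12-month mean is 12 × 48/13 = 44.3, and P(48 or more) = 0.307.

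Both readings give about 30%.

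**Comparison with the other criteria**

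- Retention: 85% is planned (15% attrition) and green is above 70%, so an on-plan trial is green.
- Uptake: the Sample size section uses 25% as its worked example and green is 15% or more, so that figure is green.
- Adherence: no planning figure is stated.

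Recruitment is the only criterion whose planning figure falls short of its green line.

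**The case against.** The strongest reply is that a green line above plan is not an error in itself. A progression threshold may reflect what a definitive trial would need rather than what the feasibility trial expects. That is a legitimate design choice, but the article does not state it, and its retention and uptake lines sit below their planning figures.

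Three further replies have some force:

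- **Rounding.** 3.69 rounds to 4. No rounding rule is given, and the criterion is written as a hard cut-off.
- **Consent versus randomisation.** The rate counts women who consent, and consent comes before baseline assessment and randomisation. Consents could reach 52 while 48 are randomised. The article plans no such surplus and uses recruitment to mean the 48.
- **Dates.** Trial design runs the study from December 2022. Enrolment from then to the start of December 2023 would be 12 months, and 48/12 = 4.00. This may be where the 4 came from, but it contradicts the 13 months stated twice.

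Some stronger readings are tempting and are not supported. A reader might infer that green is out of reach because it needs more women than the trial will enrol. The article states 48 as an aim and a plan, gives no hard cap, and 48 women within 12 months would be green. A reader might also treat amber as a partial failure that automatically triggers a protocol change. Amber is worded as a feasible outcome, recruitment is one of four criteria, and no rule says what a single amber cell sets in motion. Finally, at a true rate of exactly 4 per month the chance of 48 women within 12 months is only about 52%. That is not evidence against the threshold, because any cut-off set at the expected count of 48 gives the same figure.

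**Conclusion.** The point stands as an internal inconsistency: recruitment exactly to the stated target and timetable gives 3.69 per month and is graded amber. The conclusion rests on figures fixed in the article itself and on reading the green cut-off as written, without rounding. The figure of about 30% additionally assumes Poisson accrual at the planned rate and is an illustration only.

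The effect is modest. The gap is 0.31 per month, or 4 women over 13 months; green remains reachable if recruitment runs ahead of plan; and no safety outcome, estimate or sample size changes. It should be fixed because the table defines success, but it is not critical.

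**What to change.** Make Table 1 and the recruitment plan agree before any results are judged. There are two routes:

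1. Define green as at least 48 women recruited within the 13-month window, that is, a rate of at least 48/13 (about 3.69 per month). Define amber as more than 2 per month but below that value, which also closes the open upper end of the amber cell. Do not round the cut-off up to 3.7: 3.7 × 13 = 48.1, so an on-plan trial would still be amber.
2. Keep 4 per month and state a 12-month recruitment period consistently in the abstract and in Trial setting and recruitment.

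If a green line above plan is intended, leave the number and add a sentence saying so and giving the reason.

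The text change is one table cell, or one stated period in two places. The first route makes the green line slightly less demanding; the second commits the trial to a shorter period. Neither guarantees green: with the line set at the plan, the same Poisson assumption gives about a 52% chance. Ethics and dissemination requires ethics committee approval before a protocol modification is adopted, so an amendment is needed. Because recruitment was due to start in November 2022, the amendment should explain that it reconciles the threshold with the stated plan, so that it is not taken for a relaxation made in response to observed accrual.

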#### Qualitative substudy

Participants will be invited to take part in an optional qualitative substudy at 11–13 weeks post partum. HCPs delivering the interventions will also be invited to take part in this study.

We will undertake semistructured interviews with a subset of women from each group (ILED n=10 and best NHS Care n=10) at around 12 weeks post delivery. The final sample size will be contingent on obtaining data saturation. We will also interview a sample of HCPs involved in the delivery of care to study participants, including dieticians, obstetricians and midwives, including those with leadership and clinical managerial roles. Sampling will be purposive, aiming to obtain women from a range of ethnic groups, ages, socioeconomic backgrounds and self-reported engagement with the intervention. Participants and HCPs will be asked about their experiences and thoughts regarding the intervention, including motivating factors, and facilitators/barriers to engagement. Interviews will be conducted by a researcher from the University of Manchester/MFT who is independent of the research staff involved in the delivery and assessment of the programmes. Analysis will be conducted by two independent researchers at the University of Manchester/MFT using Braun and Clarke’s thematic analysis approach to identify key issues around the acceptability, usefulness of the programmes, and feasibility of a subsequent trial.^40^ Analysis will be inductive: open-ended, exploratory and driven by the data.

All participants will also be asked to complete an optional and anonymous end of study questionnaire developed by the study team at their postpartum visit (online supplemental file 6). This will give participants the opportunity to feedback on their experience and will enable the study team to identify improvements to the design of a possible follow-up study.

10.1136/bmjopen-2023-078264.supp6Supplementary data

#### Trial steering committee (TSC)

The TSC will include an independent consultant endocrinologist, obstetrician, dietitian and the patient representative. The committee will oversee the trial to ensure that it is carried out to the expected standards. The TSC will liaise with the CI to develop a schedule of meetings, proposed to occur every 4 months, with meetings to occur no less than annually. Minutes will be taken at TSC meetings and copies of the minutes will be filed in the Trial Master File; they will be shared with relevant stakeholders as appropriate.

### Patient and public involvement

Patient and public involvement was actively sought throughout the planning and design of this trial and continues to form a key part of the trial as it progresses. The PPIE group assisted in the development of all participant materials and provided valuable insight into the wording of participant information and acceptability of the proposed intervention. The PPIE group will be updated as the trial progresses and a further focus group will be held to advise on the interview schedule and wording for the qualitative substudy. The group will also be invited to aid in the development of summarising key findings for dissemination to relevant patient groups.

## Ethics and dissemination

This study has been approved by the Cambridge East Research Ethics Committee and is sponsored by MFT. Findings will be disseminated via publication in peer-reviewed journals, conference presentations and shared with diabetes charitable bodies and organisations in the UK, such as Diabetes UK and the Association of British Clinical Diabetologists. Anonymised data will be available on formal request once the principal results of the study have been published. Planned modifications to the protocol will be approved by the research ethics committee before they are adopted into the study. An audit trail of ethical amendments and documentation will allow monitoring by the research team and external regulatory bodies.

This is the first study to assess the feasibility and safety of an ILED in GDM as compared with best NHS care. Given the increasing incidence of GDM and associated health risks, this research is both pertinent and important. The study is not powered to show differences between ILED and best NHS care; however, the planned quantitative and qualitative assessments will inform the feasibility of the programme and a future definitive trial.
